## Abstract

**Background:**

The potential of clinical interventions, aiming at reduction of preventable Adverse Drug Events (preventable ADEs) during hospital stay, have been studied extensively. Clinical Pharmacy is a well-established and effective service, usually consisting of full-time on-ward participation of clinical pharmacists in medical teams. Within the current Hospital Pharmacy organisation in the Netherlands, such on-ward service is less feasible and therefore not yet established. However, given the substantial incidence of preventable ADEs in Dutch hospitals found in recent studies, appears warranted. Therefore, "Ward-Oriented Pharmacy", an on-ward service tailored to the Dutch hospital setting, will be developed. This service will consist of multifaceted interventions implemented in the Internal Medicine wards by hospital pharmacists. The effect of this service on preventable ADEs in elderly inpatients will be measured. Elderly patients are at high risk for ADEs due to multi-morbidity, concomitant disabilities and polypharmacy. Most studies on the incidence and preventability of ADEs in elderly patients have been conducted in the outpatient setting or on admission to a hospital, and fewer in the inpatient setting. Moreover, recognition of ADEs by the treating physicians is challenging in elderly patients because their disease presentation is often atypical and complex. Detailed information about the performance of the treating physicians in ADE recognition is scarce.

**Methods/Design:**

The design is a multi-centre, interrupted time series study. Patients of 65 years or older, consecutively admitted to Internal Medicine wards will be included. After a pre-measurement, a Ward-Oriented Pharmacy service will be introduced and the effect of this service will be assessed during a post-measurement. The primary outcome measures are the ADE prevalence on admission and ADE incidence during hospital stay. These outcomes will be assessed using structured retrospective chart review by an independent expert panel. This assessment will include determination of causality, severity and preventability of ADEs. In addition, the extent to which ADEs are recognised and managed by the treating physicians will be considered.

**Discussion:**

The primary goal of the WINGS study is to assess whether a significant reduction in preventable ADEs in elderly inpatients can be achieved by a Ward-Oriented Pharmacy service offered. A comprehensive ADE detection method will be used based on expert opinion and retrospective, trigger-tool enhanced, chart review.

**Trial registration:**

ISRCTN: ISRCTN64974377

## Background

Harmful events caused by medication are a widely recognised problem, both in hospital and outpatient settings [1-5]. These events are known as Adverse Drug Events (ADEs), usually defined as 'any injury due to the use of medication'. ADEs may occur during the normal use of medication as a result of an unavoidable pharmacological effect (side effects or Adverse Drug Reactions (ADRs)), or as a result of a medication error (preventable ADEs) [6]. Preventable ADEs are associated with substantial morbidity, increased mortality, a longer length of stay in the hospital and costs [7-9].

To increase medication safety, many interventions to reduce preventable ADEs have been studied and were found to be successful [6,10,11]. Full-time on-ward participation of clinical pharmacists in medical teams is an effective intervention in the hospital setting [12-15]. Nowadays, these services, often referred to as "Clinical Pharmacy", are routinely offered in most Anglo-Saxon countries [16-18]. In The Netherlands however, the Hospital Pharmacy organisation is mainly product-oriented. Also, most of the hospital pharmacists' time is taken up by activities such as quality assurance of medication compounding, verification of parenteral medication prepared by pharmacy technicians, therapeutic drug monitoring and medication logistics. In addition, the number of Dutch hospital pharmacists is low. On average, there are fewer hospital pharmacists per 100 hospital beds (0.75) in comparison to United Kingdome (1.42) and United States of America (14.1) [19]. As a consequence, routine clinical activities by Dutch hospital pharmacists are usually limited to off-ward services such as an on-call duty for consultations and checking of automated alerts pertaining to drug-drug interactions, drug-drug duplications and overdosages. The disadvantage of such a back-office organisation is that it gives hospital pharmacists limited insight into the relevant medication risks incurred by patients in the wards. The substantial incidence of preventable ADEs in Dutch hospitals found in recent studies [20-23] warrants an extension of the current off-ward clinical activities by an on-ward pharmacy service. To maximise its effectiveness, such a service should primarily be aimed at the highest medication risks both at patient and organisation levels. For efficiency reasons, an adaptation of Clinical Pharmacy to the Dutch hospital setting is needed because Dutch hospital pharmacists are scarce.

In this study, we choose to limit the on-ward pharmacy service to elderly hospitalised patients using five or more medications on the day of admission. Especially in elderly patients, pharmacotherapy management is challenging as polypharmacy, multi-morbidity and concomitant disabilities are often present. Altered physiological functions and cognitive decline even further increase the risk for ADEs in this vulnerable patient group [24-26]. A number of studies have described ADE incidence and preventability in elderly patients in the outpatient setting and on admission to hospitals [27-33]. However, limited data exist regarding these outcomes in the inpatient setting [34-36]. Furthermore, none of these studies have addressed the extent to which ADEs detected by the researchers were also recognised and managed by the treating physicians in the wards. Correct diagnoses in elderly patients are difficult to make because such patients often present with atypical symptoms [37]. One study found that only 51% of ADEs were recognised by the treating physicians [38]. However, the generalisability of these results to the inpatient setting is limited, because only Emergency Department physicians were involved. It thus appears that our knowledge on ADE recognition and management in the elderly inpatients is limited and further study is needed.

Numerous studies have investigated the effect of on-ward pharmacy services in the elderly hospital population by measuring surrogate end-points, such as inappropriate prescribing [39-42]. Only a few studies have measured clinical outcomes such as the number of ADEs [43,44]. However, the measurements conducted in these studies were limited to one specific type of preventable ADEs (e.g only coagulation-related) [44] or limited in the number of participants and conducted in one academic hospital [43]. Thus, the results of these studies cannot readily be generalised to other hospital settings.

The WINGS study is a multicentre study, designed to assess the reduction of ADE incidence in a high-risk population deploying limited pharmacist resources, focussing on ADE recognition and management by treating physicians, using clinical outcome as an effect measure. The on-ward pharmacy service designed in this study will be called "Ward-Oriented Pharmacy" as opposed to Clinical Pharmacy because hospital pharmacists will be attributed only part-time to this service.

The primary goals of this study are 1) to determine the number of ADEs on admission and during hospital stay in elderly patients, and to assess their causality, preventability, severity, recognition and management of ADEs by treating physicians, 2) to design and implement an effective and feasible on-ward pharmacy service for elderly patients in the Dutch hospital setting and 3) to measure the effect of this service on the incidence of preventable ADEs.

## Methods/Design

### Study design

The design is a multi-centre interrupted time series study. The interrupted time series (ITS) model follows the Cochrane Effective Practice and Organisation of Care Review Group criteria for short time series [45]. This type of series consists of pre- and post-intervention phases and needs to have at least three observation points in the pre-intervention phase and three in the post-intervention phase. Every data point needs to have at least 30 observations. The six data points needed will be strategically spread over pre- and post-measurement periods. The study will be conducted during a period of three years. An advantage of an ITS design is that it allows for the statistical investigation of potential biases such as secular trends in the estimate of the effect of the intervention [46]. ITS is also more feasible than a Randomized Controlled Trial in measuring the effect of interventions that require organisational change to a health care delivery system, which is the case in the WINGS study [45].

### Study setting

The participating hospitals are one academic hospital, the Academic Medical Centre in Amsterdam, and two non-academic hospitals, the Westfriesgasthuis Hospital in Hoorn and the Spaarne Hospital in Hoofddorp, the Netherlands. All internal medicine wards of these hospitals participate in the study.

### Study population

All consecutive patients of 65 years or older with an expected length of stay of 24 hours or longer, using 5 or more medications on the day of hospital admission and admitted to an internal medicine ward during measurement phases will be included. Patients admitted for scheduled chemotherapy, radiation therapy or transplantation, as well as patients transferred from another hospital or from a ward other than an internal medicine ward within the same hospital will be excluded. No patient will be included more than once.

### Intervention

During the whole study, all regular off-ward services, as described in the Introduction section, will be offered to Internal Medicine wards by the participating Hospital Pharmacy departments. During the intervention period, a designed Ward-Oriented Pharmacy service will be added to regular off-ward pharmacy services offered to all Internal Medicine wards of the participating hospitals. A Ward-Oriented Pharmacy service will consist of multifaceted interventions such as pharmacotherapy education, writing and implementation of drug protocols, face-to-face pharmacotherapy guidance of prescribers, participation in ward-rounds and medication reviews. Multifaceted interventions are reported to be more effective than single interventions, especially when these are complementary and not overly complex [47]. To promote implementation of a Ward-Oriented Pharmacy service, the three participating hospitals can choose different types of interventions to include in this service.

To be able to choose efficient interventions and to design a feasible Ward-Oriented Pharmacy service, the following steps will be taken:

1) An analysis of preventable ADEs based on the pre-measurement results will be conducted to identify most frequent medication risks in elderly inpatients. These risks will be categorised in patient-related medication risks and organisational medication risks. Patient-related medication risks refer to patients' characteristics, for example use of specific medication or the presence of specific co-morbidities, which might be associated with a higher risk for preventable ADEs. Organisational risks refer to ward characteristics, for example the extent to which pharmacotherapy guidelines or protocols are available and the level of existing knowledge and education. Lacking or insufficient pharmacotherapy guidelines, protocols or knowledge could entail a higher risk for preventable ADEs.

2) The results from step one will be presented to a multidisciplinary group consisting of Internal Medicine and Hospital Pharmacy staff members and residents of all three participating hospitals. These groups will prioritise risks and choose interventions tailored to local needs and possibilities to design a specific Ward-Oriented Pharmacy service. Tools and strategies like Bow-Tie risk analysis and the Swiss Cheese model [48,49] will be used to structure this process.

3) To further assure a successful implementation process, a finally designed Ward-Oriented Pharmacy service will be presented to all personnel in the participating departments. A one-month introduction period will be used to fine-tune the interventions. To keep the participating departments informed about the progress of the study, periodic evaluations will be planned and a newsletter will be distributed. After 7 months we expect the implementation of a Ward-Oriented Pharmacy service to be finalised.

### Study Outcomes

The primary outcomes of this study are 1) the number, severity and preventability of ADEs present at admission calculated per 100 hospitalisations, 2) the number, severity and preventability of ADEs during hospital stay calculated per 100 hospitalisations, 3) the percentage of ADEs recognised and appropriately managed by the treating physicians.

The secondary outcomes of this study are 1) the number of medication errors per number of medication orders and 2) the number of readmissions within three months after the index hospitalisation.

Depending on the type of the interventions that will be implemented, additional secondary outcomes will be measured to monitor the implementation of these specific interventions. For example, pharmacotherapy consultations given by hospital pharmacists on the wards can be monitored by recording the number of advices given to the physicians and nurses.

### Data collection and outcome assessment

The flow charts of the data collection process and the outcome assessment process are shown in Figures 1 and 2 and have been adapted from previous studies [50,51].

**Figure 1 F1:**
[figure not shown]
**Process of data collection and outcome assessment**. ^1 ^CPOE, Computer Physician Order Entry
^2 ^ADEs, Adverse Drug Events (preventable and non-preventable)

**Figure 3 F3:**
[figure not shown]
**ADEs included in the study**.

### Definitions

The definitions used in this study were adapted from the Glossary of Terms Related to Patient and Medication Safety by Expert Group On Safe Medication Practices [6].

*Adverse Drug Event *(ADE) is any injury occurring during the patient's drug therapy and resulting either from appropriate care, or from unsuitable or suboptimal care. ADEs include non-preventable *Adverse Drug Reactions *(ADRs) during normal use of medication, and any harm secondary to a medication error (preventable ADEs), both errors of omission and commission will be included. An ADE can result in different clinical outcomes, for example: abnormal laboratory values, worsening of the existing disease, lack of any expected disease improvement, or outbreak of new symptoms or diseases.

*Harm*: temporary or permanent impairment of the physical, emotional, or psychological function or structure of the body and/or pain resulting there from requiring intervention. In this study also abnormal laboratory values will be counted as harm.

*Medication error*: any preventable event that may cause or lead to inappropriate medication use or patient harm while the medication is in the control of the health care professional or patient. Such events may be related to professional practice, health care products, procedures, and systems, including prescribing; order communication; product labelling, packaging, and nomenclature; compounding; dispensing; distribution; administration; education; monitoring; and use.

### Sample size calculation and data analysis

The power-calculation for this study was based on the expected incidence of 15 ADEs per 100 hospitalisations and a clinically relevant 50% reduction by a Ward-Oriented Pharmacy service in the post-measurement period. This assumption was made based on the findings of two controlled studies that assessed active clinical pharmacists participation in medical teams on the wards, showing a reduction of 66% and 78% respectively [12,13]. To be able to identify a significant reduction from 15 ADEs to 7.5 ADEs per 100 hospitalisations, 496 patient admissions are needed, equally divided between pre- and post-measurement period (α = 0,05 and β = 0,8). This sample size enables to identify a reduction of 19 ADEs or more from the expected 38 ADEs in 248 admissions during the pre-measurement period.

Descriptive statistics will be used to summarise patient characteristics for the three participating hospitals and to check for any imbalance in variables between pre- and post-measurement groups. By comparing the pre- and post-measurement periods, the effect of a Ward-Oriented Pharmacy service will be analysed using a suitable generalised linear model for a short interrupted time series. Adjustment will be made for any case mix imbalances between pre- and post-measurement periods and background trend in the ADE rate over time.

Exploratory analyses are also planned to examine the effect of factors like age, sex, length of hospital stay, Charlson Co-morbidity Index Score [58], renal function on the primary and secondary outcomes. For this purpose unadjusted univariate and adjusted multivariate Poisson regression analyses are planned.

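### The 496 admissions match an undeclared one-sided 5% calculation; on a two-sided 5% reading power is about 70%, and the 0.8 printed as β is the power

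*Protocol article*

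**What the plan says.** All the relevant text is in the protocol article, under Sample size calculation and data analysis. The starting point is an "expected incidence of 15 ADEs per 100 hospitalisations", and the target is a "significant reduction from 15 ADEs to 7.5 ADEs per 100 hospitalisations". For this, "496 patient admissions are needed, equally divided between pre- and post-measurement period (α = 0,05 and β = 0,8"; an equal division is 248 per phase. The error rates appear only in that parenthesis.

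The section does not name the formula. Neither this section nor any other says whether the test is one- or two-sided. The only hint of direction is the wording of the aim ("To be able to identify a significant reduction").

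Under Study Outcomes, ADEs are numbers per 100 hospitalisations, so the outcome is a count or rate and not a yes/no result per patient. The planned effect analysis, in the same section as the sample size, is a generalised linear model for a short interrupted time series, adjusted for case-mix imbalance and background trend.

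**The concern.** An α of 0.05 with no qualifier is normally taken as two-sided. A reader who takes it so, and who sees past the β label, will conclude that the study has 80% power at two-sided 5% to detect a halving of the ADE rate. The published size does not give that. The practical risk lies in interpretation. A non-significant two-sided result would be weighed as if the chance of missing a true halving were 20%, when it is about 30% even for the simplest comparison.

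The label is a separate slip. β is the type II error, so the printed value does not describe the calculation that yields 496.

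**Working it through.** **Inputs**, all from Sample size calculation and data analysis: r1 = 0.15 and r2 = 0.075 ADEs per hospitalisation; 248 admissions per phase (496 / 2); α = 0.05; 0.8 taken as power. Sidedness and formula are not given, so both were varied.

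**1. Reproducing 496.** For two Poisson rates with the unpooled normal approximation:

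n per phase = (z_α + z_power)² × (r1 + r2) / (r1 − r2)²

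Here (0.15 + 0.075) / 0.075² = 0.225 / 0.005625 = 40.

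- One-sided 5%, 80% power: (1.6449 + 0.8416)² × 40 = 6.183 × 40 = 247.3, so 248 per phase and 496 in total. This is an exact match.
- Two-sided 5%, 80% power: (1.9600 + 0.8416)² × 40 = 7.849 × 40 = 314.0, so 314 per phase and 628 in total.

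**2. Does the conclusion depend on the formula?** Total admissions for 80% power at α = 0.05:

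| Method | One-sided | Two-sided |
|---|---|---|
| Poisson rates, difference | 496 | 628 |
| Poisson, square-root scale | 482 | 610 |
| Poisson, log rate ratio | 516 | 654 |
| Two proportions, uncorrected | 438 | 556 |
| Two proportions, continuity-corrected | 490 | 608 |
| Two proportions, arcsine | 428 | 544 |

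Unpooled proportions, log-odds and log relative risk were also tried two-sided and gave 550, 578 and 590. Across all two-sided variants the need runs from 544 to 654, and none comes within 3% of 496 (481 to 511). The variants that do (496, 490 and 482) are all one-sided.

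**3. Power with 248 per phase.** On the formula that reproduces the figure:

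z = 0.075 / √(0.225 / 248) = 0.075 / 0.03012 = 2.490

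- One-sided 5%: Φ(2.490 − 1.645) = Φ(0.845) = 0.801.
- Two-sided 5%: Φ(2.490 − 1.960) = Φ(0.530) = 0.702.

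Two-sided power by other methods: exact conditional Poisson 66.7%, log rate ratio 68.5%, square-root scale 71.4%, Fisher's exact test 71.7%, uncorrected two proportions 75.4%. The last two treat ADEs as yes/no per patient, which does not fit the outcome as defined.

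**4. The label.** Read literally, β = 0.8 means power of 1 − 0.8 = 0.2. Since 496 is recovered exactly with power 0.8, the value meant is power 0.8, that is β = 0.2.

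**The case against.** The strongest reply is that 496 is not wrong. It follows exactly from the stated rates, α and power once the test is one-sided. The aim is worded as a reduction, and a one-sided test is not an error in itself. The article is also condensed, and the full protocol or analysis plan may declare the sidedness. This stands in part: a reader might infer that 496 is an arithmetic error or that the study must recruit more, and the documents support neither. But the article chose to print the effect, α, β and N together. On the usual reading these do not fit, and the β label is wrong on any sensible reading. That is a misstatement here, not a detail left to another document.

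A second reply is that the consequence is modest. The assumed 50% reduction is smaller than the 66% and 78% that the section cites from two earlier controlled studies. On the same formula, two-sided power at 248 per phase is about 80% for a 55% reduction and about 94% for 66%. Also, 496 is given as the number needed, not as a cap, and Study population takes all consecutive eligible patients. These points are fair. They do not change the power for the 50% reduction that the section itself calls clinically relevant.

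Some stronger readings should be resisted:

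- **Power of only 20%.** This takes the misprint at face value, and the exact reproduction rules it out.
- **A planned one-sided test with a raised false-positive rate for benefit.** No section says how the final test will be done. The one-sided level is inferred from the sample size alone.
- **Wrong event counts.** The section gives "a reduction of 19 ADEs or more from the expected 38 ADEs in 248 admissions". 248 × 0.15 = 37.2, which rounded up to a whole event is 38, and 19 is half of that.
- **A specific lower power because of several ADEs per patient.** Overdispersion would reduce power, but the documents give no value for it, so no figure can be attached.

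**Conclusion.** The point holds as one of reporting. The 496 admissions correspond to 80% power at one-sided 5%, which the article does not declare. At two-sided 5% the same admissions give about 70% power (67% to 75% across methods), so the type II error is about 30% and not 20%. Two-sided 80% power would need 314 per phase on the same formula. The β label is wrong.

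This rests on three assumptions: the stated rates of 0.15 and 0.075, Poisson variation with independent admissions, and an unadjusted comparison of 248 with 248. That the original calculation was one-sided Poisson is an inference from an exact match, since the formula is not named. Neither 80% nor 70% is the power of the planned time-series model. Adjusting for a background trend would ordinarily lower power further, but the documents give nothing from which to size that loss.

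**What to change.** In Sample size calculation and data analysis:

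1. Replace the β entry with power 0.8 (β = 0.2).
2. State that the 496 figure comes from a one-sided 5% comparison of two Poisson rates, unadjusted for trend or case mix. If the sponsor's records show another formula, name that one instead.
3. Report beside it that two-sided 5% power with 248 per phase is about 70% for the same unadjusted comparison.

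Whether the final test is one- or two-sided remains the sponsor's choice; the text should make clear which level the quoted power refers to. The cost is a sentence or two. Enrolment and conduct do not change, but the stated power becomes less favourable.

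### The 496 admissions give 80% power only if admissions are independent: the figure allows nothing for variation between hospital-by-time-point batches

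*Protocol article*

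**What the plan says.** The Study setting section names three hospitals, all of whose internal medicine wards take part. The Intervention section adds the service for whole wards and allows that "the three participating hospitals can choose different types of interventions to include in this service". Under Study design, "The six data points needed will be strategically spread over pre- and post-measurement periods", and each point must hold at least 30 observations.

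The section on sample size and analysis starts from an "expected incidence of 15 ADEs per 100 hospitalisations" and aims to detect a "significant reduction from 15 ADEs to 7.5 ADEs per 100 hospitalisations" with "α = 0,05 and β = 0,8" (the second figure can only be meant as power 0.80). It concludes that "496 patient admissions are needed, equally divided between pre- and post-measurement period". For the analysis, "the effect of a Ward-Oriented Pharmacy service will be analysed using a suitable generalised linear model for a short interrupted time series". Two adjustments are named: case mix and background trend. Hospitals otherwise appear in that section only in the descriptive statistics. It gives no ICC or design effect.

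**The concern.** Exposure to the service is set by hospital and calendar time, never by patient. Admissions at one hospital around one measurement point share staff, residents and local practice, so their ADE counts may move together. Neither a linear trend nor case-mix covariates absorb the scatter of such batches around the trend.

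If that scatter exists, 248 admissions per period carry less information than 248 independent ones, and the stated power is too high. If the model's standard error also ignores it, an ordinary high or low batch near the interruption is read as evidence about the service. The sample size is fixed before the study, so an analysis plan written later can correct the standard error but cannot restore the power.

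**Working it through.** **Inputs from the article:** rates 0.15 and 0.075; 248 admissions per period; alpha 0.05; power 0.80; three hospitals; six points.

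**Assumed, because the article does not give them:** every hospital contributes equally to every point (3 × 6 = 18 batches, m = 496/18 = 27.6); residual batch ICC of 0.01 to 0.05.

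**Step 1, reproduce 496.** Difference of two independent Poisson rates, one-sided 5%, 80% power:

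n per period = (1.645 + 0.842)² × (0.15 + 0.075) / 0.075² = 247.3, rounded up to 248; total 496.

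This matches exactly, with no design effect. The same formula two-sided gives 628. The event counts agree too: 248 × 0.15 = 37.2, in line with "a reduction of 19 ADEs or more from the expected 38 ADEs in 248 admissions".

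**Step 2, allow for batches.**

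- Design effect: DE = 1 + (27.6 − 1) × ICC.
- One-sided power at 496: Φ(0.075 / √(DE × 0.225/248) − 1.645).
- True size of a test that ignores DE: two-sided 2[1 − Φ(1.96/√DE)]; one-sided 1 − Φ(1.645/√DE).
- The simulated column is an unscaled Poisson model with hospital, linear trend and step terms on 18 batches, gamma batch effects, no true effect, 1,000 runs per row.

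| ICC | DE | N needed (496 × DE) | Power at 496, one-sided | Size, two-sided formula | Size, two-sided simulated | Size, one-sided formula |
|---|---|---|---|---|---|---|
| 0 | 1.00 | 496 | 80% | 5% | 5.1% | 5% |
| 0.01 | 1.27 | 628 | 71.5% | 8.2% | 7.8% | 7.2% |
| 0.02 | 1.53 | 760 | 64.3% | 11.3% | 9.9% | 9.2% |
| 0.05 | 2.33 | 1,155 | 49.5% | 19.9% | 18.6% | 14.1% |

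A separate simulation with 3,000 runs per setting gave two-sided sizes of 8%, 11% and 19% at ICC 0.01, 0.02 and 0.05.

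**Step 3, which standard error repairs the size.** The same null simulation with errors scaled by the Pearson dispersion and a t reference:

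- Shocks independent across hospitals: scaling on 18 batches brings the rate to 4.5% to 4.7%, and scaling on six pooled points to about 4% to 5%.
- Shocks shared by all hospitals at a time point (a season, for example): scaling on 18 batches still gives about 8% to 10%, 12% to 14% and 21% at ICC 0.01, 0.02 and 0.05, across separate runs. The six pooled points give about 5% to 6%.

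**Step 4, the trend term.** Step 2's power has no trend in it, but the article commits to adjusting for one. With six equally spaced points, the squared correlation between the step and time is 0.75² / (0.25 × 35/12) = 0.771, so the variance of the step is multiplied by 1/(1 − 0.771) = 4.4. On the log scale, expected z = ln 2 / √[(1/37.2 + 1/18.6) × 4.4] = 0.693/0.596 = 1.16. Two-sided power is then about 21%, even at ICC 0. Simulation of the trend-adjusted model gave 22%.

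**The case against.** The strongest reply concerns the analysis. The article asks for a suitable model for a short interrupted time series and does not name its family, unit, dispersion or variance estimator. Poisson regression is named only for the exploratory analyses. A design built on six data points fits an aggregated analysis equally well, and such detail commonly sits in a full protocol or analysis plan. This stands. A reader might infer that the planned model counts 496 independent admissions and so has a false-positive rate of 8% to 19%. The article does not say so, and a dispersion-scaled fit would hold the rate near 5% if shocks are independent across hospitals.

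Two further inferences also fail:

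- Different services in different hospitals do not raise the false-positive rate, because under the null none of them works.
- Stable differences between hospitals do not raise it either, because each hospital appears in both periods (simulated 4.5% to 6.1%).

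A pooled average effect of a locally tailored service is also a legitimate target. Hospital-level steps would rest on about 248/3 = 83 admissions per period, or about 83 × 0.15 = 12 events against 83 × 0.075 = 6. That is too few to tell which service worked.

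The ICC and the 18 equal batches are indeed assumptions. What the reply does not reach is the sample size: 496 is stated, is reproduced under independence, and leaves no room for batch variation.

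**Conclusion.** The point holds for the sample size and only conditionally for the test. The stated 80% power is that of a one-sided comparison of 248 with 248 independent admissions. With a residual hospital-by-point ICC of 0.01 to 0.05, it becomes about 72% to 50% before any trend adjustment. If the ICC is zero, this loss disappears.

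The 8% to 19% false-positive range (7% to 14% one-sided, 5% at ICC 0) needs all of the following: that ICC range, 18 equal batches, and an unscaled Poisson model adjusted only for hospital, case mix and trend. It shows what an unspecified variance could cost and is not an established property of this plan.

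**What to change.** In the section on sample size and analysis:

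1. State that 496 gives 80% power only for independent admissions. Show power over a range of assumed ICCs for the trend-adjusted model that is actually planned.
2. Specify hospital terms and standard errors that allow for overdispersion between batches: Pearson scale not below 1, with a t reference on the residual degrees of freedom.
3. Add a sensitivity analysis on the six pooled time points, because scaling on 18 batches does not protect against shocks common to all hospitals. With 6 − 3 = 3 residual degrees of freedom it will have little power, so it serves as a check and not as the main test.
4. Show each hospital's pre-post change descriptively beside the pooled effect, without claiming that it identifies which service worked.

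**Cost.** This is wording and recalculation, with no new patients or data. The price is wider intervals and a less favourable stated power. In simulations of the trend-adjusted model with a 50% reduction, moving from unscaled to scaled errors on 18 batches lowered rejection from 22% to 13% at ICC 0 and from 31% to 12% at ICC 0.05. Part of the 31% reflects the inflated size of the unscaled test.
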